#### REVISION HISTORY

| Revision | Originator | Date Effective | Nature of Change                             |
|----------|------------|----------------|----------------------------------------------|
| A        | [name]  | 4 June 2014    | Initial Release                              |
| B        | [name]  | 10 June 2014   | Incorporation of [name] / Lineagen edits |
| C        | [name]  | 11 June 2014   | Incorporation of [name] edits                |

|                   |                                                                                                                 |                      |
|-------------------|-----------------------------------------------------------------------------------------------------------------|----------------------|
|                   | Clinical Study Protocol                                                                                  |                      |
|                   | Title: Establishing the Clinical Utility (ECU) of First Step Dx PLUS and NextStep Dx PLUS |                      |
| Supersedes: Rev B | Document Number: Rev C                                                                                          |                      |
|                   | Effective Date: 11JUNE14                                                                                        | Page: 5 of 20 |

### ACRONYMS

|      |                                |
|------|--------------------------------|
| ASD  | Autism spectrum disorder       |
| CMA  | Chromosomal microarray         |
| CPV® | Clinical Performance and Value |
| DD   | Developmental delay/disability |
| ID   | Intellectual disability        |
| SD   | Standard deviation             |

|                   |                                                                                                                 |                      |
|-------------------|-----------------------------------------------------------------------------------------------------------------|----------------------|
|                   | Clinical Study Protocol                                                                                  |                      |
|                   | Title: Establishing the Clinical Utility (ECU) of First Step Dx PLUS and NextStep Dx PLUS |                      |
| Supersedes: Rev B | Document Number: Rev C                                                                                          |                      |
|                   | Effective Date: 11JUNE14                                                                                        | Page: 6 of 20 |

## STUDY SYNOPSIS

**Protocol Title** Establishing the Clinical Utility (ECU) of First StepDx PLUS and NextStepDx PLUS Study

**Background** The American Academies of Pediatrics, Neurology and Child and Adolescent Psychiatry consider the genetics evaluation part of the comprehensive assessment of individuals with disorders of postnatal development including developmental delay (DD) autism spectrum disorder (ASD), and intellectual disability (ID). Due to the added clinical detection rate of chromosomal microarray analysis (CMA) over basic genetic testing technologies (such as standard karyotyping), in 2010, the American College of Medical Genetics recommended CMA as a first-tier diagnostic genetic evaluation. Lineagen's diagnostic genetic test, FirstStepDx PLUS, includes the **most comprehensive, whole-genome CMA** currently available for clinical use. It has a two-fold increase in detection rate for variants that underlie ASD (from 5-7% on typical CMA platforms to 12-14% on FirstStepDx PLUS; Matsunami et al. 2013, Matsunami, et al 2014) and an overall increase in detection rate (from 15- 20% to over 30%). Once a genetic diagnosis is obtained, screening and management of associated life-threatening medical risks (seizures, tumors, renal disease, heart disease), administration of indicated medications and therapies, and avoidance of contraindicated treatments can be implemented (Coulter and Irons and Ellison references).

Appropriate assessment of new health care interventions or technologies requires information on the clinical utility, economic value, affordability, and public health benefits of these interventions (Phillips et al. 2014; Peabody et al. forthcoming). Clinical utility—demonstrating the usefulness of a test for clinical practice—is now the most significant hurdle facing diagnostic technology companies. Today, without scientific evidence of clinical utility, even the most promising technologies may not be covered and reimbursed by payors.

**Study Objective** To determine if use of FirstStepDx PLUS and Next StepDx PLUS are associated with higher clinical quality, less variability in clinical practice, and lower costs from decreased resource utilization.

**Study Design** The study uses a randomized controlled study design of pediatric neurologists and developmental pediatricians and front-line (primary care) pediatricians. Physicians will be randomly assigned to a control or one of two intervention arms.

- Pre-intervention/baseline assessment: will be done using pediatric CPV® vignettes and a physician questionnaire to both control and intervention arms.
- Intervention: 2-4 weeks after baseline introduce FirstStepDx PLUS and NextStepDx PLUS to the intervention group of doctors using a webinar format to describe the application and utilization of the two assays.

|                   |                                                                                                                 |                      |
|-------------------|-----------------------------------------------------------------------------------------------------------------|----------------------|
|                   | Clinical Study Protocol                                                                                  |                      |
|                   | Title: Establishing the Clinical Utility (ECU) of First Step Dx PLUS and NextStep Dx PLUS |                      |
| Supersedes: Rev B | Document Number: Rev C                                                                                          |                      |
|                   | Effective Date: 11JUNE14                                                                                        | Page: 7 of 20 |

Post-intervention: 4 weeks post-intervention, a second round of pediatric CPV® vignettes will be administered to both control and intervention arms. FirstStepDx PLUS results will be available to order as part of the vignettes and results will be presented as a downloadable PDF for intervention group 1; FirstStepDx PLUS and NextStepDx PLUS will be available for physicians in intervention group 2.

## Study instruments

The Clinical Performance and Value Vignettes (CPV®) used in this study simulate a clinical encounter for individuals with an atypical phenotype and clinical presentation indicative of a possible genetic disorder. Each physician will respond to open-ended questions regarding the clinical care they would provide for that patient. These responses are scored in five domains (taking a medical history, conducting a physical examination, ordering appropriate tests, making a diagnosis, and prescribing treatment and therapies against explicit evidence and criteria as determined by the literature and medical associations. Results are presented as percentage correct. Each case will take approximately 15 minutes to complete. All case responses will be completed online and kept confidential.

A questionnaire will also be administered to all physicians at the beginning of the first round of CPV vignette data collection. This questionnaire will assess physician and practice characteristics.

## Outcome Measures

### Primary Outcome

- Difference in combined diagnostic and treatment CPV® domain score post-intervention versus baseline comparing intervention and control groups

### Secondary Outcomes

- Difference in utilization of appropriate treatment including indicated versus unnecessary therapy pre- and post-intervention between intervention and control groups
- Difference in utilization of laboratory testing such as fluorescence *in situ* hybridization (FISH) analyses, global assessment, and utilization of other laboratory tests pre- and post-intervention, between intervention and control groups
- Difference in overall Clinical Performance and Value Vignettes (CPV®) scores post-intervention versus baseline between intervention and control groups

## Study Population

225 specialists and general pediatricians (specialists include pediatric neurologists and developmental pediatricians) will be recruited and invited to participate in the study. 70% of the sample will be comprised of specialist physicians and 30% of primary care pediatricians.

Inclusion eligibility criteria cover:

- A minimum of 2 years post residency, no more than 30 years in practice
- Board-certified
- No prior use of either the FirstStepDx PLUS or NextStepDx PLUS assays

|                   |                                                                                                                 |                      |
|-------------------|-----------------------------------------------------------------------------------------------------------------|----------------------|
|                   | Clinical Study Protocol                                                                                  |                      |
|                   | Title: Establishing the Clinical Utility (ECU) of First Step Dx PLUS and NextStep Dx PLUS |                      |
| Supersedes: Rev B | Document Number: Rev C                                                                                          |                      |
|                   | Effective Date: 11JUNE14                                                                                        | Page: 8 of 20 |

- Minimum threshold of pediatric patients currently being treated: >30 patients

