**Physician Recruitment**

Providers will be contacted by recruitment letter sent via USPS and then by email and/or telephone. A dedicated script will be used to assess eligibility and willingness to participate. Physicians will be randomly selected from lists of approximately 5,000 specialists and 25,000 general pediatricians. Physician privacy and confidentiality will be maintained in accordance with HIPAA regulations.

Informed consent will be obtained by having physicians read the consent and provide their signature and date and time of consent. Once this is obtained, physicians will be considered enrolled into the study.

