**Sample Size**

The study is adequately powered to detect differences in the combined diagnosis and treatment score as measured by the CPVs®. A sample size of 75 in each arm (225 total) provides over 80% power to detect an estimated 6-7% difference in scores with alpha=0.05. Due to possible attrition, extra subjects may be enrolled to ensure that at least 225 subjects will be used in the analysis.

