**Data Analysis**

Summary statistics will be determined for all variables. Simple cross tabulations will be prepared as part of the data resolution process. The calculation of basic descriptive statistics is used to check distributions and find outliers and out-of-range data. Numerical variables will be characterized in terms of means and standard deviations or by medians and interquartile range for skewed or highly non-normally distributed variables. For hypothesis testing, tests will be conducted at a two-sided  $\alpha = 0.05$ .

With experimental data we can estimate the effect of FirstStepDx PLUS or the sequential testing of FirstStepDx PLUS and NextStepDx PLUS on the primary outcomes comparing treatment and control groups. We will use a difference in difference analysis approach comparing differences between groups before and after intervention. We will control for all potential confounders, including physician-level characteristics, such as age, gender, specialty, years in practice, and practice-level characteristics—multi- versus single specialty practice, rural/urban location, and payor mix.

|                   |                                                                                                                 |                      |
|-------------------|-----------------------------------------------------------------------------------------------------------------|----------------------|
|                   | Clinical Study Protocol                                                                                  |                      |
|                   | Title: Establishing the Clinical Utility (ECU) of First Step Dx PLUS and NextStep Dx PLUS |                      |
| Supersedes: Rev B | Document Number: Rev C                                                                                          |                      |
|                   | Effective Date: 11JUNE14                                                                                        | Page: 9 of 20 |

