## 2. STUDY DESIGN

The study is an interventional longitudinal study design of physician practice. 225 specialist and general pediatricians without previous exposure to FirstStepDx PLUS or NextStepDx PLUS will be selected from a nationally representative list of approximately 25,000 board-certified pediatricians and 5,000 specialists. These physicians will be **randomized** into one of three arms: to receive information regarding FirstStepDx PLUS (“Intervention A”), to receive information about FirstStepDx PLUS and NextStepDx PLUS (“Intervention B”) for use in clinical practice, and controls not receiving any intervention.

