Round 2 of data collection, or post-intervention assessment, will occur 4 weeks after the introduction of the intervention.

CPV scores will be used to compare baseline practice with practice post-intervention in the 3 different physician groups/arms.

This study will test the following hypotheses:

1. Clinical practice, specifically decisions around treatment of individuals with disorders of postnatal development including DD, ASD, and ID will vary widely among all physician types. This documentation of variation in practice will demonstrate the need for a new diagnostic service that FirstStepDx PLUS and NextStepDx PLUS would fulfill.
2. FirstStepDx PLUS and NextStepDx PLUS will improve the quality and appropriateness of care and therapeutic plans, as measured by the number of physicians that correctly act on the results of the assay.

This hypothesis will be tested through total of 9 CPVs consisting of 3 CPVs cases for each of 3 case archetypes as follows.

- Case A: Patients who are currently undiagnosed and for whom FirstStepDx PLUS or would initiate appropriate therapy
- Case B: Patients who are wrongly—or incompletely—diagnosed and for whom FirstStepDx PLUS would change therapy (i.e., terminate inappropriate or unnecessary therapy and initiate appropriate therapy)
- Case C: Patients who are undiagnosed by FirstStepDx PLUS testing and for whom NextStepDx PLUS testing would initiate appropriate therapy and/or earlier intervention will result in better outcomes

The CPVs™ will be randomly assigned to physicians for each to complete 3 CPVs™ (one from each type). Each of the CPVs™ will be scored by physicians for changes in clinical practice including treatment changes, frequency of follow up, laboratory tests and imaging studies ordered - see for scoring sheet.

|                   |                                                                                                                 |                       |
|-------------------|-----------------------------------------------------------------------------------------------------------------|-----------------------|
|                   | Clinical Study Protocol                                                                                  |                       |

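### Specialty defines the 70/30 recruitment quota, but the protocol names no stratification by it and the written primary model averages the effect over it; stratifying and reporting by specialty is a cheap improvement

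*Protocol*

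**What the plan says.** The synopsis, under Study Population, sets the mix: "70% of the sample will be comprised of specialist physicians and 30% of primary care pediatricians". Under Physician Recruitment it gives the source: "Physicians will be randomly selected from lists of approximately 5,000 specialists and 25,000 general pediatricians". Section 2 repeats the source without the quota, saying that physicians "will be selected from a nationally representative list of approximately 25,000 board-certified pediatricians and 5,000 specialists".

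Allocation is described briefly: "Physicians will be randomly assigned to a control or one of two intervention arms". Sections 2 and 2.1 add that there are three groups of 75. No stratification factor is named, and none is ruled out.

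For the analysis, the synopsis lists "physician-level characteristics, such as age, gender, specialty, years in practice" among the variables to be controlled for. Section 8.2 then writes out the primary model as TIME, INTERV, TIME x INTERV and control variables. It lists those controls twice. Neither list contains specialty; the nearest entry is whether the practice is single or multispecialty, which describes the practice and not the physician. There is no interaction between specialty and anything else.

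**The concern.** Specialty is the one physician characteristic that the design itself fixes, so it is the natural stratification factor and a natural model term. As written it is neither. Two things follow.

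First, the primary care share can drift between arms by chance. If specialists and generalists change differently from Round 1 to Round 2 for reasons unrelated to the intervention, such as learning the vignette format, that difference leaks into the arm contrast. The adjustment promised in the synopsis would not stop this.

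Second, each reported arm effect is an average over a 70/30 mix. A reader who wants to know whether the assays change practice among primary care pediatricians, or among specialists, cannot tell from the written model.

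**Working it through.** **The plan's own figure.** The synopsis states: "A sample size of 75 in each arm (225 total) provides over 80% power to detect an estimated 6-7% difference in scores with alpha=0.05". No SD is given, so the figure can be neither confirmed nor refuted. The largest SD consistent with 80% power, two-sided 5%, is difference x sqrt(75/2) / (1.960 + 0.842). This is 13.1 for 6 points and 15.3 for 7. I use the 6-point case as the reference, where the standard error of an arm contrast is 6 / 2.802 = 2.14 points.

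**The quota.** 0.70 x 225 = 157.5 specialists and 0.30 x 225 = 67.5 generalists, or 52.5 and 22.5 per arm. The sampling fractions are 157.5/5,000 = 3.15% and 67.5/25,000 = 0.27%, a ratio of 11.7. Against their share of the combined list (5,000/30,000 = 16.7%), specialists are over-represented 70/16.7 = 4.2-fold. This is context only; it does not affect the validity of the comparison between arms.

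**Why a specialty main effect does not help.** When every physician contributes both rounds, the TIME x INTERV coefficient for an arm is the mean change in that arm minus the mean change in controls. Specialty has the same value in both rounds and cancels from each physician's change. If generalists change by d points more than specialists regardless of arm, and the arms' primary care shares differ by g, then g x d stays in the contrast whether or not a specialty main effect is fitted. In a simulated balanced two-round panel the interaction coefficients were identical with and without the main effect (0.654609 and -0.419974). A specialty x TIME term is what removes g x d. This exact cancellation belongs to the linear model for CPV score; it does not carry over automatically to the logistic and Poisson models.

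**How often the arms drift.** Take 67 generalists among 225, p = 0.298. The SD of the difference in primary care share between two arms of 75 is sqrt(2 x 0.298 x 0.702/75 x 225/224) = 7.5 percentage points. With 75 per arm, a gap of 10 points or more means at least 8 physicians. Results from simulated random allocations:

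| Gap in primary care share | Chance |
|---|---|
| 10 points or more, one given pair of arms | about 18% |
| 10 points or more, at least one of the three pairs | about 37% |
| 15 points or more, at least one of the three pairs | about 10% |

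**What that is worth in score points.** The documents give no value for d; I assume 4 points.
- A 10-point gap: 0.10 x 4 = 0.4 points. A 15-point gap: 0.15 x 4 = 0.6 points.
- A typical (1 SD) gap: 0.075 x 4 = 0.3 points, which is (0.3/2.14)^2 = about 2% of the contrast variance.
- With d = 0, nothing.

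**What by-specialty reporting can deliver.** Assume the same effect (6 points) and SD (13.1) in both strata, with the pooled contrast at exactly 80% power.
- Specialists: standard error 13.1 x sqrt(2/52.5) = 2.56; power = Phi(6/2.56 - 1.96) = 65%.
- Generalists: standard error 13.1 x sqrt(2/22.5) = 3.91; power = Phi(6/3.91 - 1.96) = 34%; 95% half-width 1.96 x 3.91 = 7.7 points.

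**The case against.** Much of the opposing case stands.

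- **The protocol is silent on stratification; it does not exclude it.** A randomisation plan or analysis plan not shown here may provide for it, and by-specialty subgroups are often placed there. So one can say only that no stratification is named. But the model equation and covariate lists are in the protocol, the two statements about specialty disagree there, and an analysis plan written later cannot stratify a completed randomisation.
- **A quota does not bias a randomised contrast.** This is correct, and sampling a smaller group more heavily is ordinary practice.
- **The imbalance is small in score points.** Also correct: about 2% of the contrast variance under the assumed 4-point difference. The case for stratifying rests on its low cost, not on a large expected error.

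A reader might infer two stronger things. One is that the result is wrong for the population on the list and should be reweighted to it. The documents do not support this. Section 2 calls the list representative, not the sample, and no objective or endpoint defines a list-average effect. Headcount weights of 1/6 and 5/6 would be the reviewer's choice of target. They would carry a design effect of 0.7 x (0.167/0.7)^2 + 0.3 x (0.833/0.3)^2 = 2.35, cutting 75 per arm to an effective 32 or so.

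The other is that the protocol itself expects the effect to differ by physician type. Its first hypothesis says that practice "will vary widely among all physician types". That predicts variation in current practice and is used to argue the need for the tests; it says nothing about who benefits more.

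**Conclusion.** The point holds as a low-cost improvement, not as a flaw that threatens the primary comparison. Three facts are documented: a 70/30 quota by specialty, no named stratification by specialty, and a primary model that averages over specialty while omitting it from covariate lists where the synopsis says it belongs. The last is an inconsistency to reconcile in any case.

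The practical size is modest. A gap of 10 points or more in primary care share arises in about 18% of allocations for a given pair of arms, worth about 0.4 points if change differs by 4 points between physician types. The 4 points are an assumption, and the effect scales with it down to zero. The imbalance figures assume simple random allocation into arms of exactly 75. The power figures assume equal effect and SD in both strata and a pooled contrast at exactly 80%.

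**What to change.** 1. **Section 2:** carry the 70/30 quota into the body and randomise within two strata, specialist and primary care, in permuted blocks (about 52-53 specialists and 22-23 generalists per arm).
2. **Section 8.2, primary model:** add specialty and specialty x TIME to the control variables, so that the text agrees with the synopsis and any remaining imbalance in change is adjusted for.
3. **Section 8.2, secondary estimates:** report arm effects by specialty from a separate model with TIME x INTERV x specialty, with confidence intervals and labelled secondary.
4. **Interpretation:** state in one sentence that the pooled effect describes a 70/30 specialist/primary care mix.

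The cost is two randomisation lists instead of one, one extra table and no extra physicians. The generalist estimates will be imprecise: about 22 per arm, roughly 34% power if the pooled contrast has 80%. An inconclusive generalist result must therefore not be read as no effect.
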